**Methods and analysis:**

In this retrospective cohort study, we will link general practice records from the UK Clinical Practice Research Datalink Aurum database. We will establish a cohort of patients diagnosed with SMI between 1998 and 2020 who are matched with up to four controls on age, sex, general practice and calendar year. We will use multivariable mixed-effects linear regression models and Cox proportional hazard models with sequential adjustment for potential confounders identified by separate directed acyclic graphs.

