#### Comparison group

The unexposed represents the counterfactual and will include patients without an SMI Read code ever (hereafter *unexposed*) drawn from the source population. Up to four unexposed matches will be selected at baseline only if they have a qualifying weight Read code within±one year of the index date to the exposed in which they are matched. The matching variables include: age, sex, practice and calendar time. All weight Read codes will be extracted.

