### Confounding

We have identified confounding variables using directed acyclic graphs (DAGs), which aims to theoretically formalise potential confounders, colliders and biasing relationships.^26^ The DAG for each objective is described in online supplemental material S1. The DAG for objective 1 shows one direct path from the exposure (ie, SMI) to the outcome (ie, weight change), and four indirect paths: via health behaviours (ie, alcohol use, smoking and diet), SES status, psychotropic medication, and healthcare access and provision. Diet and physical activity are latent variables in CPRD Aurum because they are unmeasured. There are three confounding paths: via age, sex and ethnicity.^27 28^ Thus, the minimally sufficient adjustment for the total effect of SMI status on weight is to adjust for age, sex, and ethnicity.

10.1136/bmjopen-2021-053427.supp1Supplementary data

Frequency matching will ensure our ability to adjust for confounding variables that include age, sex, and calendar year, and matching on practice will remove practice-specific variables. In addition, we will fully adjust our models by considering several covariates in the relationship between the exposure and outcome (see table 2). All categorical variables will be analysed using the natural reference category as the reference group. Data on individual prescriptions for psychotropic and cardio-metabolic medications will be extracted from the primary care data from index date until censoring. For psychotropic medications, drugs will be classified according to the British National Formulary. For objectives 2 and 3, we will assess the impact of weight gain on change in cardio-metabolic risk factors and incidence of CVD using mediation analysis to allow us to estimate the direct (unmediated) and indirect (mediated) effects of SMI on CVD risk and incidence. To do this, we will fit two regression models: one regressing the outcome on the exposure, adjusting for confounders and another regressing the mediator on the exposure and confounders using the Stata *Med4way* command to estimate mediated effects.^29^ For objective 4, we will assess the presence of confounding by comparing estimates with and without adjustment. We will use Read codes, which have been previously developed by our team, to identify outcome and covariate records.

**Table 2 T2:** Confounders

Confounders and covariates		Measures

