#### Primary analyses

For objectives 1 and 2, the outcome will be visually inspected by plotting trajectories of weight and cardio-metabolic risk factor change using all repeated measurements for patients with SMI versus patients without SMI. For these analyses, we will use a mixed-effects linear regression model including terms for SMI, time and their interaction to estimate regression coefficients with 95% CIs by SMI status. Models incorporating psychotropic medications will analogously include medication-time multiplicative interaction terms. We will include a random effect for individual and practice identifier to account for intra-class correlation resulting from common practice membership. Diagnostic tests will be conducted to confirm linear regression assumptions are met including linearity of residuals, residual normality using quantile–quantile (Q–Q) plots, and residual heteroscedasticity using residual versus fitted value plots. We will assess for exploratory subgroup effects by adding interactions (eg, by age, sex, ethnicity and SES) and, if significant, we will assess the strength of the associations in separate subgroups for clarity. For objective 2, we will model the association between weight and cardio-metabolic change using restricted cubic splines to allow for non-linear associations. For objective 3, we will use Kaplan-Meier survival estimates for the exposed and unexposed groups to estimate the distribution of time from index date to total and fatal CVD and mortality (all-cause). The statistical equivalence of the two curves will be examined using the log-rank test. This analysis will use a survival from index date between the exposed and unexposed groups using an adjusted Cox proportional hazards regression model with follow-up time as the timescale. Restricted cubic splines will be computed with five knots to visually explore non-linear associations between the exposure and the outcomes. For objective 4, we will use a Poisson regression examining person-time to estimate the rate at which patients who received weight management services over the study period in patients with SMI compared with patients who do not have SMI, adjusting for confounders and BMI.

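### The SMI-by-time estimate for objectives 1 and 2 is not adjusted for ethnicity unless ethnicity also interacts with time

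*Protocol article*

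**What the plan says.** The Outcomes section and Table 1 define objective 1 as change in weight or BMI, and objective 2 as change in cardio-metabolic risk factors. Primary analyses gives the model for both: a "mixed-effects linear regression model including terms for SMI, time and their interaction to estimate regression coefficients with 95% CIs by SMI status". It then names one more kind of time interaction: "Models incorporating psychotropic medications will analogously include medication-time multiplicative interaction terms". The random part is a term for individual and one for practice. The only other interactions are exploratory: "We will assess for exploratory subgroup effects by adding interactions (eg, by age, sex, ethnicity and SES"), followed up in separate subgroups if significant.

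On adjustment, the Confounding section finds three confounding paths for objective 1 and concludes that "the minimally sufficient adjustment for the total effect of SMI status on weight is to adjust for age, sex, and ethnicity". It adds that the models will also be fully adjusted for the Table 2 covariates. The abstract announces sequential adjustment. Under Comparison group: "The matching variables include: age, sex, practice and calendar time". Ethnicity is not among them.

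**The concern.** With repeated measurements on each person, the SMI-by-time coefficient compares rates of change. A covariate fixed at baseline does not vary within a person. Its main effect takes up differences in level and has almost no hold on the slope. If the model is fitted with only the time interactions that the article names, ethnicity is in the model but does not adjust the estimate that answers the question about change.

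Two things are at stake. The reported slope could carry confounding by ethnicity while being described as adjusted for the minimally sufficient set. And the step from the crude to the minimally adjusted model would hardly move the slope however strong that confounding was, which a reader could take as evidence that there is little of it. The cohort is large (a feasibility count of 135 870 patients with SMI), so precision will be high and a small bias need not be hidden by the confidence interval.

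**Working it through.** **The plan's own figures.** The article gives no numerical figure for the objective 1 and 2 models. Its sample size (3907) concerns CVD incidence and has no bearing here.

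**Formula.** Let S be SMI (0/1), t time, and C an indicator for an ethnic group. Suppose the mean outcome is

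b0 + b1·S + b2·t + b3·S·t + g·C + d·C·t.

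If C has prevalence p1 in the exposed and p0 in the unexposed, the average slopes are b2 + b3 + d·p1 and b2 + d·p0. Without the C·t term, the SMI-by-time coefficient therefore estimates about

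b3 + d·(p1 − p0).

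The term g·C does not enter this expression, so the bias is d·(p1 − p0) with or without the main effect. For several ethnic categories it is the sum of such products. If matching makes p1 = p0, it is zero.

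**Inputs.** The documents give neither d nor p1 − p0 for ethnicity, so both are assumed and varied. From the article: mean follow-up 4.6 years, median 3.2 years (Sample size calculation), and up to four unexposed per exposed patient (Comparison group).

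**Simulation.** Random-intercept models were fitted to simulated repeated weights.

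- Set A: 10,000 exposed and 40,000 unexposed; exponential follow-up with mean 4.6 years, clipped to 1–15 years; about 1.0 v 0.5 records per year; between-person SD 15 kg; residual SD 3 kg; covariate effect on level 3 kg; true SMI-by-time effect 0; 20 replicates.
- Set B: 4,000 exposed and 16,000 unexposed; yearly measurements over 5 years; true SMI-by-time effect 0.30 kg/year; 15 replicates.

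Mean SMI-by-time estimates in kg/year:

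| Set | Prevalence, exposed v unexposed | d | True value | d·(p1 − p0) | No covariate | Main effect only | Main effect and C-by-time |
|---|---|---|---|---|---|---|---|
| A | 25% v 15% | 0.2 | 0 | 0.020 | 0.022 | 0.022 | 0.002 |
| A | 30% v 15% | 0.3 | 0 | 0.045 | 0.047 | 0.046 | 0.001 |
| A | 50% v 30% | 0.5 | 0 | 0.100 | 0.101 | 0.101 | 0.001 |
| B | 20% v 10% | 0.5 | 0.30 | 0.050 | 0.352 | 0.352 | 0.302 |
| B | 40% v 20% | 0.5 | 0.30 | 0.100 | 0.396 | 0.396 | 0.297 |
| B | 40% v 20% | −0.5 | 0.30 | −0.100 | 0.198 | 0.198 | 0.296 |
| B | 60% v 30% | 0.5 | 0.30 | 0.150 | 0.446 | 0.446 | 0.296 |
| B | matched, equal prevalence | 0.5 | 0.30 | 0 | 0.301 | 0.301 | 0.301 |

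The main effect changes the estimate by 0.001 at most. The time interaction brings it back to within 0.004 of the true value. The bias follows the formula in size and sign, so it can go either way. A matched covariate causes none.

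**Scale over follow-up.** Over the 3.2-year median, the three biases of set A come to 0.022 × 3.2 = 0.07 kg, 0.047 × 3.2 = 0.15 kg and 0.101 × 3.2 = 0.32 kg.

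**Which covariates this reaches.**

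- Age and sex: matched, so balanced at baseline.
- Ethnicity: in the minimal set and not matched.
- Smoking and alcohol: placed by the Confounding section on indirect paths from SMI to weight, not on confounding paths.
- SES: also on an indirect path. Data linkage and the footnote to Table 2 define it as practice-level deprivation, which matching on practice balances. The Discussion speaks of patient-level deprivation, so the article is not consistent here.

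**The case against.** The strongest reply is that the gap is inferred. The list of model terms is introduced as what the model includes, it leaves out the covariates altogether, and nowhere does the article say that they enter as main effects only. A condensed article may leave such detail to the full plan. This stands as a caution. But the article does specify this model's time interactions, and it adds one by analogy for medication. That makes the omission for the confounders more than ordinary brevity.

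Second, interactions with ethnicity are planned. If they were built up hierarchically from SMI-by-time, an ethnicity-by-time term would come with them. Their form is not stated, however. They are exploratory, are followed up only if significant, and address effect modification. They do not enter the primary estimate.

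Third, a reader might infer more than the documents support:

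- That the slope is unadjusted for age and sex as well. Matching deals with both at baseline, and the matched run shows no bias.
- That every Table 2 covariate confounds the slope. Under the plan's own diagram, leaving health behaviours and SES without time terms does not bias the total effect. It means only that a slope labelled fully adjusted is not adjusted for them.
- That all steps of the sequential adjustment must give nearly the same slope. The medication-by-time term can move the fully adjusted one.
- That the bias is known to be large. Carried over 10 years, the most extreme case of set A is about 1 kg (0.101 × 10), but its inputs are assumed and the median follow-up is 3.2 years. The simulated data had no person-to-person variation in slope, so bias expressed in simulated standard errors would look too decisive.

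**Conclusion.** The point holds for ethnicity. Followed as written, the model leaves the SMI-by-time estimate essentially unadjusted for a confounder that the plan itself says must be adjusted for and that matching does not balance. That a main effect does not repair this follows from the structure of the model and does not depend on the assumed inputs. The size does: about 0.02 to 0.10 kg/year, or 0.07 to 0.32 kg over the median follow-up, for prevalence differences of 10 to 20 percentage points and slope effects of 0.2 to 0.5 kg/year, in either direction. If ethnicity had no effect on rate of change, or were equally distributed in the two groups, there would be no bias.

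The minimal set is stated in the article for weight. For objective 2 the diagram is in a supplement that is not shown, and the same conclusion applies there in so far as ethnicity is a confounder. This should be settled before the models are fitted. It does not put the design in doubt.

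**What to change.** In Primary analyses, state that ethnicity enters the objective 1 and 2 models with both a main effect and an interaction with time, in the same functional form of time as the SMI-by-time term. Treat age and sex in the same way, as protection against incomplete matching and follow-up that differs between the groups. Report the SMI-by-time contrast at each adjustment step.

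If the fully adjusted models are meant to adjust the slope for smoking, alcohol and SES, give those covariates time interactions too, and say that the result is then no longer the total effect. Baseline BMI-by-time should not be required: baseline BMI is close to the baseline value of the outcome, and conditioning the slope on it changes what is estimated.

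The cost is a change of wording, a few more fixed effects from data already to be extracted, longer tables, and a very small loss of precision (standard error up to about 2% larger in set A).

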### Exposures

For all analyses, the exposure of interest is SMI. We will extract information on the study cohort up to censoring. Extracted information includes the diagnosis date and type, which will be grouped according to the two major SMI subgroups as classified by the ICD-10: F20-29 non-affective psychotic disorder (ie, schizophrenia, schizotypal and delusional disorders, psychosis not otherwise specified) and F30-39 affective psychotic disorder (ie, bipolar, manic, schizoaffective disorders, major depressive disorder with psychosis). Patients may have Read codes in the primary care data relating to both non-affective and affective psychotic disorders. These will be classified using the most recent Read code because we will assume that the latest diagnosis is the correct one. For example, it is common for diagnoses to be clarified over time from first episode psychosis to schizophrenia. Based on similar studies, instances where there are Read codes relating to both diagnoses at the same date will be coded under non-affective psychotic disorder.^25^ Data on individual prescriptions for psychotropic medication will be extracted from the primary care data from index date until censored.

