Health behaviours	Smoking status	Categorical (0=never; 1=ex-smoker; 2=current smoker (light: 1–9 cigarettes/day; moderate: 10–19 cigarettes/day; heavy: 20+ cigarettes/day)). This is coded in GP records. We will use the most recent recorded value of smoking status at the study start date.
	Alcohol use	Continuous (units per week). This is coded in GP records. We will use the most recent recorded value of alcohol use at the study start date.
Demographics	Socioeconomic status (SES)*	Categorical (quintiles)
	Ethnicity†	Categorical (white; Asian or Asian British; black or black British; other ethnic group, mixed)
	Sex†	Binary (0=male; 1=female)
	Age at study entry, in years	Continuous
Physical and/or medical factors	Baseline weight status (body mass index (BMI))	Categorical (normal weight (BMI 18.5–24.9 kg/m^2^); overweight (25.0–29.9); obese (30.0–34.9); severe obesity (35.0–35.9); morbid obesity (40.0–44.9)
	Psychotropic medication	Categorical (antipsychotics (first-generation and second-generation); antidepressants; mood stabilisers)
	Cardio-metabolic medication	Categorical (blood glucose lowering medications; antihypertensive treatments, statins)
We include the following additional variables for objectives 3 and 4 only		
CVD risk factors	Total cholesterol/HDL ratio	Continuous
	Systolic and diastolic blood pressure	Continuous
	Glycaemia	HbA1c/fasting blood glucose (FBG)

*This variable is grouped according to practice level Index of Multiple Deprivation. This is an indicator of material deprivation based on income; employment; health deprivation and disability; education, skills and training; crime; barriers to housing and services; and living environment. It is categorised as quintiles 1–5 with 1 being the most deprived and 5 being the least deprived.

†This variable is grouped according to recommendations by the UK Office for National Statistics.^33 34^

CVD, cardiovascular disease; GP, general practitioner; HbA1c, haemoglobin A1c; HDL, high-density lipoprotein.

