### Statistical analysis

Analyses will be conducted in Stata using an estimation approach. We do not intend to impute missing data. The entry date into the analysis is the index date. The outcome date is the earliest of: (1) the date of death or (2) date of diagnosis of the outcome of interest. For objectives 1 and 2, we will use all repeated measures and run separate models for each analyses. For objective 3, we will use the first recorded diagnosis of the outcome of interest rather than recurrent events. Patients who do not have the outcome of interest will be censored at the earliest of: (1) date of death, (2) date of leaving the practice, (3) date of the latest download of data or (4) the study end date.

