#### Descriptive summaries

Frequency matching will reduce potential confounding and balance the baseline characteristics of the *exposed* and *unexposed* on age, sex, practice and calendar year. Adequacy of matching will be confirmed by comparing means using independent t-tests. Descriptive statistics will describe the baseline characteristics of patients in the cohort. Categorical data will be presented as frequency and percentages, and continuous variables will be summarised using descriptive statistics mean, standard deviation (SD) or median and interquartile range (IQR). Comparisons between the groups will be made using χ^2^ tests and t-tests (or Wilcoxon rank-sum tests) as appropriate. Length of exposure and the most commonly prescribed class of psychotropic for each patient will be summarised. The causes of death will be categorised as CVD and all-cause mortality.

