Since the study is descriptive, any association observed would not imply an SMI diagnosis is causative of adverse physical health outcomes. However, we might assume the greater the magnitude of the observed association the less likely it is due to bias and more likely due to a causal process.^32^ Furthermore, diet and physical activity are unmeasured confounders because they are unobserved in CPRD Aurum. Similarly, other unmeasured confounders like poverty may place people with SMI at increased risk of homelessness, which has consequences on healthcare access and provision. We address this potential confounding by linking to patient level IMD as a proxy measure of SES, but acknowledge this may not fully capture deprivation and leaves room for residual confounding. Moreover, information bias may be present since the CPRD Aurum relies on a GP recording of health outcomes. Furthermore, we can only examine primary care prescriptions. Any prescribing solely within secondary care may not be included as this was not historically routinely recorded in GP records. Thus, it is possible we will miss the first prescription(s). Finally, physical health checks are not always performed on random samples of the population, and it is possible that more regular testing is done on people with overweight and obesity. We expect that some patients will have incomplete information recorded. However, by determining what proportion of patients do not have appropriate information recorded, we can evaluate the scale of these problems, and highlight the need for improved recording for continuity of care between healthcare professionals.

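### Psychotropic medication is, on the natural reading, modelled against time since SMI diagnosis and not time since the drug was started, so differences between drug classes could reflect start dates

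*Protocol article*

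**What the plan says.** Under Primary analyses, the protocol article fits, for objectives 1 and 2, a "mixed-effects linear regression model including terms for SMI, time and their interaction". The next sentence extends this to drugs: "Models incorporating psychotropic medications will analogously include medication-time multiplicative interaction terms". Clustering is handled thus: "We will include a random effect for individual and practice identifier".

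Under Statistical analysis, "The entry date into the analysis is the index date"; Study cohort defines the index date as the first SMI Read code. Duration of follow-up allows up to 22 years.

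Table 2 (under Confounding) codes medication by class only: "Categorical (antipsychotics (first-generation and second-generation); antidepressants; mood stabilisers". Under Exposures, "Data on individual prescriptions for psychotropic medication will be extracted from the primary care data from index date until censored". Time on drug appears only under Descriptive summaries: "Length of exposure and the most commonly prescribed class of psychotropic for each patient will be summarised". No section puts time since first prescription, or duration of use, into a model.

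**The concern.** For the exposed group SMI begins, by definition, at time zero, so SMI by time is a sensible term. A drug has no such common origin: one patient may start at index, another years later, and either may switch or stop. Carrying the same product term over to medication describes the drug's effect as a straight line in years since diagnosis, whatever the start date.

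The Introduction says trials link these drugs to rapid weight gain and that the longer course is unclear. A straight line on the index clock cannot separate an early rise from a later course when start dates vary. The Discussion says the results could inform medication choice if drugs differ meaningfully. A class mostly used first and a class mostly used later could then appear to differ even if they act identically.

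**Working it through.** The article gives no figure for the medication models and no drug effect in kg. The sizes below are therefore illustrations under stated assumptions.

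**1. Which clock.** The only time origin stated for the analysis is the index date. The SMI-by-time term uses it, and the medication term is built by analogy with that term. Time since index is therefore the natural reading, although the article does not say so outright.

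**2. Steady gain, by algebra.** Let a drug started *s* years after index add *g* kg per year on drug. While on drug its effect is g(t − s) = −gs + g·t.
- The slope on the index clock is *g* for any *s*.
- The main effect, read at t = 0, is −gs. With g = 1 it is +2 kg for s = −2 and −4 kg for s = 4.
- Simulation with current-use coding and 5 years of follow-up agrees: slopes 0.92 to 1.04 kg/year, main effects from +2.22 to −3.60 kg.

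**3. Rapid gain, then plateau, by algebra.** Let the drug add *G* kg in its first year and nothing after. With follow-up to *T*, the average gain per year on drug is G/(T − s). Take G = 4.
- T = 6: 4/6 = 0.67 kg/year for s = 0; 4/2 = 2.0 for s = 4.
- T = 3: 4/3 = 1.33 kg/year for s = 0; 4/1 = 4.0 for s = 2.

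The start date alone changes the slope. Fitted slopes are smaller, because the line is fitted to all on-drug weights, most of them on the plateau, together with a level term.

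**4. The same case, simulated.** Assumptions: 4 kg in year one and then flat; 60% treated; half-yearly weights; background 0.3 kg/year; between-person SD 10 kg, residual SD 2 kg; random intercept for patient, practice effect omitted. Early starters begin in months 0–6. Late starters begin in years 3–5 (6-year follow-up) or at 1.5–2.5 years (3-year follow-up, close to the article's median of 3.2 years).

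| Follow-up, coding | Term | Early start | Late start |
|---|---|---|---|
| 6 y, current use | medication × time (kg/y) | 0.29 | 1.20 |
| 6 y, current use | main effect (kg) | +2.74 | −3.03 |
| 6 y, ever use | medication × time (kg/y) | 0.47 | 0.69 |
| 3 y, current use | medication × time (kg/y) | 1.00 | 2.77 |
| 3 y, current use | main effect (kg) | +1.52 | −4.97 |
| 6 y, time since start | first-year gain (kg) | 4.00 | 4.01 |

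A second simulation gave current-use slopes of 0.30 against 1.15 (6 years) and 1.12 against 2.92 (3 years).

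**5. Two identical drugs in one model.** Assumed 5 kg in year one and then flat, 5 years, current use; A started at index, B at 2 years. A: +3.31 kg and 0.70 kg/year. B: −1.35 kg and 1.58 kg/year. B's negative main effect lies outside its period of use: at t = 2, when B begins, its fitted effect is −1.35 + 2 × 1.58 = +1.81 kg.

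**6. Can the slope change sign?** With a gain that never reverses and a single start time, the lowest slope was −0.006 (SE 0.014). A clear change needed an assumed later loss of 0.3 kg/year: over 5 years, −0.23 for a start two years before index, against +0.44 to +4.81 for starts at 0 to 4 years.

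**7. Time since start.** For the 5 kg plateau drug, two linear pieces (first year, later) gave first-year gains of 5.13 to 5.47 kg over 5 years and 4.71 to 5.10 kg over 10 years, for starts at 0, 1, 2 or 3 years. Later slopes ran from −0.14 to 0.01 kg/year, all within about one SE of zero.

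**The case against.** **The clock is inferred.** The article never defines time in the mixed models, nor whether medication is baseline, ever or current use, and a condensed article may leave such coding to a fuller plan. This stands as a limit on certainty. It does not remove the point, because the article does choose a functional form by analogy and names no other clock. Both codings show the distortion in the plateau case.

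**Opposite-signed effects.** A reader might infer that identical drugs would get effects of opposite sign. That is not supported for the interaction term the article names. The sign change is in the main effect, which for late starters is an extrapolation back to index, before the drug was begun.

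**Start date as the sole cause.** A reader might also infer that estimates depend only on when a drug was prescribed, or that the effect is forced to be proportional to time since diagnosis. Neither holds. The slope distortion needs a gain that flattens, which is assumed, and with a steady gain and current-use coding the slope hardly moves. A model with a medication main effect has a level as well as a slope.

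**Medication is secondary.** SMI is the stated exposure, medication is a covariate on an indirect path, and no objective compares drugs. This lowers the weight of the point, but the Introduction and Discussion both promise medication findings.

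**The alternative is imperfect.** Prescriptions are extracted only from index, and the Discussion concedes "it is possible we will miss the first prescription(s". The good recovery in the simulations is also favourable, since the fitted pieces match the assumed shape. Both objections stand and shape the fix.

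**Conclusion.** The concern holds in limited form. On the natural reading, drugs that begin at different times are placed on the SMI-index clock, and no term for time on drug is planned. If gain is rapid and then flattens, an identical drug's medication-by-time slope differs about four-fold between early and late starters over 6 years (1.20/0.29 = 4.1) and nearly three-fold over 3 years (2.77/1.00 = 2.8). These ratios rest on current-use coding, an assumed 4 kg first-year gain and assumed start dates; with ever-use coding the 6-year contrast is smaller (0.69/0.47 = 1.5). Under a steady linear gain with current-use coding the slope is little affected. The point bears on comparisons between drug classes. It does not show that the SMI-by-time estimate without medication is wrong. The plan should be changed before class differences are offered as a guide to medication choice.

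**What to change.** In Primary analyses, replace the medication sentence with wording that:
- states the time scale of the objective 1 and 2 models;
- enters medication as a time-updated exposure by class, with a flexible term (spline or linear pieces) for time since first recorded prescription of that class, alongside time since index;
- reports the estimated change at fixed times after starting, instead of a slope per year since diagnosis;
- flags patients already on the class at or soon after index, or restricts a sensitivity analysis to apparent new users, because earlier prescriptions are not extracted and first ones may be missed.

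The cost is plan wording and programming; dated prescriptions from index onward are already to be extracted. The drawbacks are a larger model and some misdating of drug start, which should be acknowledged with the results.
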